### Adverse events

Every adverse event (AE) that occurs during the trial will be faithfully recorded and evaluated to assess the associations between AEs and the experimental interventions or evaluations. Necessary measures will be taken immediately for the safety of the participates and to determine whether to stop the intervention. If any AEs occur during the study, the investigator will take necessary measures according to the patient’s condition in a timely manner.

### Outcome measures

The study will be conducted over a period of 12 months. All outcomes will be assessed at baseline and after the 12-month intervention. In total, one primary outcome indicator and four secondary outcome indicators will be analysed:The primary outcome indicator is the change in the largest Cobb angle.

It is recommended that the magnitudes of the scoliotic curves are measured using the Cobb method. The Cobb angle will be measured on the standing frontal radiograph according to the Cobb method by a physician specializing in the treatment of scoliosis.2)The secondary outcome measures will be as follows:The sagittal index (SI) is the sum of the plumbline distances at C7 and L3. When SI<60 mm, the back is considered flat; 60–95 mm is in the normal range; and > 95 mm is considered kyphosis [20].Forced vital capacity (FVC) is an established measure of pulmonary function.Peak oxygen uptake (VO_2_peak) is recognized as the best expression of exercise endurance and will be measured by cardiopulmonary exercise testing.Quality of life will be evaluated by the Scoliosis Research Society-22 (SRS-22) questionnaire. This questionnaire was specifically designed for patients with scoliosis and consists of 22 items addressing 5 dimensions: function/activity, pain, self-image, mental health, and satisfaction with treatment. The higher the score is, the better the outcome.

### Data management

All the involved participants were coded with a number. We used a case report form (CRF) to record the information of participants, including basic information,

X-ray results, functional evaluation results, and follow-up. The data will be collected by a blinded physiotherapist, other researchers will be forbidden from obtaining the research data. Besides, statisticians will be blinded in our study.

### Sample size calculation

The primary outcome indicator is the change in the largest Cobb angle. We calculated the sample sizes using the formula below:$$\mathrm{n}1=\mathrm{n}2={\left[\left({\mathrm{Z}}_{2\alpha }+{\mathrm{Z}}_{2\beta}\right)\ast \mathrm{S}/\delta \right]}^2$$Mild AIS: α = 0.05, Z_2α_ = 1.645;β = 0.10, Z_2β_ = 1.282. The previous clinical results showed that the combined standard deviation of the Cobb angle of the two groups was δ = 6.1°and S = 7.48 [21]. Based on these results, in this study, the sample size needed for each group was determined to be 26 cases if patients are included in the TDCET group and the CE group at a ratio of 1:1. Twenty percent more subjects will be required to allow adjustments for other factors, such as withdrawal, missing data, and loss to follow-up. It is recommended that a minimum of 33 subjects per group are included for mild IS comparisons.Moderate AIS: α = 0.05, Z_2α_ = 1.645; β = 0.10, Z_2β_ = 1.282. The previous clinical results showed that the combined standard deviation of the Cobb angle of the two groups was δ = 2.82°and S = 3.75 [22]. Based on these results, in this study, the sample size needed for each group was calculated to be 31 cases if patients are included in the TDCET group and the CE group at a ratio of 1:1. Twenty percent more subjects will be required to allow adjustments for other factors, such as withdrawal, missing data, and loss to follow-up. It is recommended that a minimum of 39 subjects per group are included for moderate IS comparisons.

Hence, 66 patients with mild IS and 78 patients with moderate IS will be included.

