### Statistical analysis

All statistical procedures will be performed according to the principles of intention-to-treat (ITT). Outcome assessor will be blinded after assignment to interventions. A linear mixed model will be used to identify the differences between the TDCET group and the CE group in the change of the largest Cobb angle, SI, FVC, VO_2_peak and SRS-22 questionnaire scores across the periods of assessment (intervention factors and time) in the mild and moderate subgroups. The Risser sign will be considered a covariate. When necessary, post hoc comparisons will be performed using the Bonferroni correction for multiple comparisons. The correlations between the clinical variables (Cobb angle) and secondary variables (SI, FVC, VO_2_peak and SRS-22 questionnaire scores) will be assessed. All data will be analysed using SPSS v.23.0 software. *P* < 0.05 will be considered statistically significant.

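### The sample sizes rest on a one-sided 5% critical value while the analysis tests undirected differences at P < 0.05; on a two-sided reading, power is about 82–84% per stratum, not 90%

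*Protocol article*

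**What the plan says.** The section "Sample size calculation" of the protocol article sizes each severity stratum separately, on the change in the largest Cobb angle. The inputs for mild disease are "Mild AIS: α = 0.05, Z_2α_ = 1.645;β = 0.10, Z_2β_ = 1.282", and those for moderate disease are "Moderate AIS: α = 0.05, Z_2α_ = 1.645; β = 0.10, Z_2β_ = 1.282". The formula is printed as n1 = n2 = [(Z_2α + Z_2β) × S/δ]².

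For mild disease the text reports that "the combined standard deviation of the Cobb angle of the two groups was δ = 6.1°and S = 7.48". For moderate disease the corresponding figures are δ = 2.82° and S = 3.75. The results are that "the sample size needed for each group was determined to be 26 cases" in the mild stratum and that "the sample size needed for each group was calculated to be 31 cases" in the moderate stratum. An allowance of 20% for withdrawal, missing data and loss to follow-up raises these to 33 and 39 per group, or 66 + 78 = 144 patients in all.

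The section on statistical analysis says that a linear mixed model "will be used to identify the differences between the TDCET group and the CE group", separately in the mild and moderate subgroups, and that P "< 0.05 will be considered statistically significant". Neither section says whether the test is one-sided or two-sided.

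**The concern.** The value 1.645 cuts off 5% in one tail, which corresponds to a two-sided level of 10%. A search for differences, with no direction given, at P < 0.05 is ordinarily a two-sided 5% test, for which the critical value is 1.96. If so, the sample size belongs to a more lenient test than the one to be run, and the stated beta of 0.10 is not achieved in either stratum. At stake is the chance of missing a true effect of the planned size on the primary outcome.

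Two further defects sit in the same paragraph. The printed formula lacks the factor 2 that a comparison of two independent means needs, so a reader who applies it does not obtain the stated numbers. The text also presents δ as part of a combined standard deviation, and so never identifies it as the between-group difference that the formula requires.

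**Working it through.** **Inputs** (all from the sample size section):

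| | Mild | Moderate |
|---|---|---|
| δ (degrees) | 6.1 | 2.82 |
| S | 7.48 | 3.75 |
| d = δ/S | 0.8155 | 0.752 |
| Evaluable n per group | 26 | 31 |
| Enrolled n per group | 33 | 39 |

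Both strata use 1.645 and 1.282, which sum to 2.927.

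**Step 1. The formula as printed**, [(Z + Z) × S/δ]²:

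- Mild: (2.927 × 7.48/6.1)² = 12.9, so 13 per group.
- Moderate: (2.927 × 3.75/2.82)² = 15.1, so 16 per group.

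Neither agrees with the plan.

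**Step 2. The plan's figures reproduced**, with the factor 2, 2[(Z + Z) × S/δ]²:

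- Mild: 2 × 12.88 = 25.8, so 26; 26/0.8 = 32.5, so 33.
- Moderate: 2 × 15.15 = 30.3, so 31; 31/0.8 = 38.75, so 39.

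All four stated figures appear. The calculation was therefore one-sided at 5%, with a factor 2 that was used but not printed.

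**Step 3. The same calculation for a two-sided 5% test** (1.960 + 1.282 = 3.242):

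- Mild: 2 × (3.242 × 7.48/6.1)² = 31.6, so 32 evaluable per group (33 by t test).
- Moderate: 2 × (3.242 × 3.75/2.82)² = 37.2, so 38 evaluable per group (39 by t test).

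**Step 4. Two-sided power at the planned evaluable numbers.** By normal approximation, power = Φ(d√(n/2) − 1.96):

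- Mild: Φ(0.8155 × √13 − 1.96) = Φ(2.940 − 1.96) = Φ(0.980) = 84%.
- Moderate: Φ(0.752 × √15.5 − 1.96) = Φ(2.961 − 1.96) = Φ(1.001) = 84%.

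The t-test figures use the noncentral t distribution with 2n − 2 degrees of freedom:

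| Setting | Mild | Moderate |
|---|---|---|
| One-sided 5%, n = 26 / 31, normal | 90.2% | 90.6% |
| One-sided 5%, n = 26 / 31, t | 89.5% | 90.0% |
| Two-sided 5%, n = 26 / 31, normal | 84% | 84% |
| Two-sided 5%, n = 26 / 31, t | 82.2% | 83.0% |
| Two-sided 5%, n = 33 / 39 (no loss), normal | 91% | 91% |
| Two-sided 5%, n = 33 / 39 (no loss), t | 90.4% | 90.6% |

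**Step 5. Type II error.** At 26 and 31 evaluable it is about 16–18% per stratum, against the stated 10%. The strata are different patients, so the chance that both comparisons succeed is about 0.822 × 0.830 = 68%, against 0.90 × 0.90 = 81% as planned. The protocol does not require both to succeed, so this joint figure is only an illustration.

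**The case against.** The strongest reply is that the sidedness of the final test is stated nowhere, so the mismatch is inferred. The hypothesis in the Background, that the exercises are effective, is directional. The subscripts 2α and 2β can be read as two-tailed areas of 0.10 and 0.20, which makes 1.645 and 1.282 consistent with a deliberate one-sided 5% design. An analysis plan that is not shown might say so. If that was the intention, the 90% stands. This is a real limit. But an aim worded as effectiveness does not specify a test, and a one-sided 5% rule would need to be declared and justified, because readers will take P < 0.05 as two-sided. On either reading the text needs correction, and the missing factor 2 and the labelling of δ do not depend on sidedness.

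A second reply is that 82–84% describes an unadjusted two-sample comparison, whereas the plan is a mixed model with the Risser sign as covariate. The gain from adjustment cannot be computed from the document. If the covariates correlated 0.3 with the outcome (an assumption), two-sided t-test power at 26 and 31 would be about 86%; at 0.5 it would be about 91–92%. This stands as a caveat, but the plan's calculation takes no credit for adjustment, so its 90% does not rest on it.

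A third reply is that the 20% is an allowance, not a forecast. With about 10% loss (29–30 and 35 per group) two-sided t-test power is about 86–87%, and with no loss it is just over 90%. That is correct, but 26 and 31 evaluable is the basis on which the plan itself sets beta = 0.10. The same surplus cannot serve both to cover losses and to make up for the critical value.

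It is also fair to say that the factor 2 is a reporting slip that changes no planned number, and that two-sided power stays above 80% even after the full allowance is used.

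**Conclusion.** The concern holds. The stated 26 and 31 per group follow only from a one-sided 5% critical value with an unprinted factor 2. For a two-sided 5% test, which is the ordinary reading of the analysis section, power at those numbers is 82% and 83% by t test, or 84% in both strata by normal approximation, instead of 90%. The two-sided design reaches about 90% only if every one of the 33 and 39 enrolled per group is evaluable. These figures take the plan's δ and S as given, equal groups, and a simple comparison of two means. They also assume that no one-sided test was intended; if one was, the power stands but the test must be declared and justified. The formula as printed is wrong in any case, since it yields half the stated sample size.

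**What to change.** - In the statistical analysis section, state that the primary comparison in each stratum is tested at two-sided 5%.
- In the sample size section, print n per group = 2[(Z_α/2 + Z_β) × S/δ]², with Z_α/2 = 1.96. Identify δ as the assumed between-group difference in the change of the largest Cobb angle, and S as the standard deviation.
- Restate the power as about 82–84% with 26 (mild) and 31 (moderate) evaluable per group, and about 90% only if none of the 33 and 39 enrolled per group is lost.

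The cost is wording, and a less favourable power statement. Enrolment can stay at 144. Keeping 90% two-sided power after a 20% loss would be a different choice: 32/0.8 = 40 and 38/0.8 = 47.5, so 48 per group, or 80 + 96 = 176 patients by normal approximation. Correcting the text does not require that.

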### Statistical analysis

All statistical procedures will be performed according to the principles of intention-to-treat (ITT). Outcome assessor will be blinded after assignment to interventions. A linear mixed model will be used to identify the differences between the TDCET group and the CE group in the change of the largest Cobb angle, SI, FVC, VO_2_peak and SRS-22 questionnaire scores across the periods of assessment (intervention factors and time) in the mild and moderate subgroups. The Risser sign will be considered a covariate. When necessary, post hoc comparisons will be performed using the Bonferroni correction for multiple comparisons. The correlations between the clinical variables (Cobb angle) and secondary variables (SI, FVC, VO_2_peak and SRS-22 questionnaire scores) will be assessed. All data will be analysed using SPSS v.23.0 software. *P* < 0.05 will be considered statistically significant.

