Some experts propose PSSEs as compensatory strategies with bracing to prevent potential adverse effects on the muscles and spine as well as to increase brace effectiveness. Moreover, PSSEs can be used as a stand-alone treatment with milder curves to avoid bracing. The latest review concluded that insufficient evidence is available to suggest that PSSEs with or without other conservative treatments can reduce the Cobb angle and improve trunk appearance and balance, [10] and three other reviews of studies conducted between 2005 and 2020 suggested that the few clinical trials on the effects of PSSEs on scoliotic deformities that exist are of low quality [11–13]. Surprisingly, Cantele et al. affirmed that quality of life and self-perception can be impaired in scoliotic girls, especially when they practise PSSEs, because PSSEs are often perceived by adolescents as stressful, boring and limiting to other everyday activities, even when specific exercise programmes may help prevent scoliosis curve progression and improve their health and fitness status when routinely performed [14].

Three-dimensional corrective exercises (TDCEs) for scoliosis are based on the theory of PSSEs and are characterized by the combination of outpatient treatment and home-based exercise: 1) the outpatient treatment component includes three-dimensional self-correction, stabilization of the corrected posture, stretching, manual fascia relaxation therapy, and breathing training, and 2) the home-based exercise component includes active self-correcting exercises combined with basic body awareness therapy. However, according to data from previous randomized controlled trials (RCTs) regarding exercise or bracing, RCTs are not very feasible because of ethical reasons and the high rate of families refused randomization and stated preference for one treatment over the other [15, 16]. Ferriter et al. reported that a non-randomized controlled trial (non-RCT) of high quality can produce outcomes that approximate those found in RCTs [17]. Therefore, a non-RCT was designed to test the following hypothesis: TDCEs are effective in patients with either mild or moderate IS.

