### Participant recruitment

Both mild and moderate IS patients from the outpatient clinic will be recruited and stratified by disease severity. Experienced clinicians will divide the participates who meet the inclusion criteria into mild or moderate subgroups according to Cobb angle on the anteroposterior and lateral whole-spine X-rays in the standing position taken at the first visit. Written informed consent will be obtained from participants who meet all the inclusion and none of the exclusion criteria and the parents. Then, participants will be assigned to two age- and sex-matched groups. No further recruitment measures will be taken, and no individuals with a direct relationship with the researchers, such as students/staff of the hospital or close relatives, will be included. Patient enrolment started in November 2020 and is scheduled to end in December 2021.

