### Quality control and quality assurance

It is necessary to take appropriate measures to minimize bias because confounding bias is a key factor that can affect the quality of test results. Unified training and assessments will be conducted for participating researchers, and only strictly normative data will be used to reduce measurement bias.

In addition, the advantages and characteristics of the study will be explained to the subjects in detail before enrolment so that the participants and/or their parents will fully understand the possible benefits, thereby improving compliance and reducing withdrawal from the study.

It is necessary to use a three-grade quality control system: the researchers will conduct self-examinations of the cases they have included, the inspectors from each subgroup will supervise the assessments every month, and the inspectors from the research group will supervise the assessments every quarter.

A comprehensive Data and Safety Monitoring Board will be established to ensure the quality of each step during the testing process as much as possible. The Clinical Research Unit (CRU) is an independent committee responsible for controlling the quality and ensuring the safety of this study to ensure the safety of the subjects and the validity of the data. According to the outcomes, data quality, and evidence of AEs, the trials can be terminated if the intervention is considered useless or invalid. If AEs occur, the main investigator will decide whether to suspend the intervention in this study according to the patient’s condition. In addition, the DMC can terminate the trial if the data are found to be invalid or useless.

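### The primary model of this non-randomised comparison names only the Risser sign as covariate; entered as a main effect it would not change the treatment contrast, and on any reading baseline Cobb angle within stratum and curve site are not adjusted for

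*Protocol article*

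**What the plan says.** All of the following is in the protocol article.

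- **Allocation** (Participant recruitment): "Then, participants will be assigned to two age- and sex-matched groups". There is no randomisation. The Background defends this with ethical reasons and with experience from earlier randomised trials, namely "the high rate of families refused randomization and stated preference for one treatment over the other".
- **Severity** (Participant recruitment; Eligibility criteria): "Both mild and moderate IS patients from the outpatient clinic will be recruited and stratified by disease severity". Mild is 10 to under 25 degrees and moderate is 25 to under 45 degrees.
- **Timing** (Outcome measures): "All outcomes will be assessed at baseline and after the 12-month intervention".
- **Primary outcome** (Sample size calculation): "The primary outcome indicator is the change in the largest Cobb angle".
- **Model** (Statistical analysis): a linear mixed model with intervention and time factors, fitted within the mild and moderate subgroups. On covariates it says only: "The Risser sign will be considered a covariate".
- **Confounding** (Quality control and quality assurance): the section states that "confounding bias is a key factor that can affect the quality of test results". The measures that follow are researcher training and data standards, which the text itself links to measurement bias.

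**The concern.** Without randomisation, comparability of the groups rests on the design controls and the adjustment in the model. The article regards confounding as important, but its analysis names a single covariate in a model where that covariate may have no effect on the quantity of interest.

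The treatment effect in a mixed model with group and time is the group-by-time term. A baseline characteristic that does not vary over time alters that term only if it interacts with time, or if the response is the change or the 12-month value. The article does not say which is meant. Baseline curve size within each stratum and curve site are not named in any form. Age and sex are used for matching but do not appear in the model. If the groups differ systematically on any of these, and they predict 12-month change, the difference enters the treatment estimate.

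**Working it through.** **Numbers available.** The planned sizes reproduce as 2 × [(1.645 + 1.282) × S/δ]², with the factor 2 that the printed formula omits:
- mild: 2 × (2.927 × 7.48/6.1)² = 25.8, so 26 per group and 52 evaluable; 26/0.8 gives 33 recruited per group;
- moderate: 2 × (2.927 × 3.75/2.82)² = 30.3, so 31 per group and 62 evaluable; 31/0.8 gives 39 recruited per group.

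**Step 1: what a main effect does.** Let G be group, t = 0 or 1 for visit, R the Risser sign and u a child-level random intercept:

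y = μ + αG + βt + θGt + γR + u + e.

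The within-child difference is D = y(12 months) − y(baseline) = β + θG + (difference in errors). R has dropped out. With both visits observed, the estimate of θ is the difference in mean change, with or without R.

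**Step 2: forms that do adjust.** Adding a Risser-by-time term gives D = β + θG + λR, which is the regression of change on group and Risser. If change is itself the response, each child has one value, so neither a time factor nor a random intercept can be estimated. The model reduces to that same regression, and Risser does adjust.

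**Step 3: numerical check.** 150 data sets were simulated with 33 children per arm and no true treatment effect. Assumed values: mean Risser 0.8 lower in one arm; true baseline Cobb 1.5 degrees higher in that arm at equal Risser; change falling by 1.0 degree per Risser grade and rising by 0.15 per degree of true baseline Cobb; between-child SD of true Cobb 3.5; baseline measurement SD 2. Average estimates, in degrees (truth 0):

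| Analysis | Estimate |
|---|---|
| Group × time, no Risser | 1.039 |
| Group × time + Risser main effect | 1.039 |
| Group × time + Risser × time | 0.326 |
| Change on group + Risser | 0.326 |
| Change on group + Risser + baseline Cobb | 0.535 |
| 20% of follow-up missing at random, no Risser | 1.000 |
| 20% missing, Risser main effect | 1.004 |

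With complete data the first two rows agreed in every data set to about 4 × 10⁻¹⁴. With missing follow-up the largest difference in any one data set was 0.13 degrees.

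**Step 4: why baseline Cobb did not help here.** Adjusting for Risser alone leaves an expected bias of 0.15 × 1.5 = 0.225. The slope of change on *measured* baseline is (0.15 × 3.5² − 2²)/(3.5² + 2²) = (1.84 − 4)/16.25 = −0.133, negative because of measurement error. Adding measured baseline then gives an expected 0.225 + 0.133 × 1.5 = 0.42. The simulated 0.326 and 0.535 are these values plus simulation error. So in non-equivalent groups, adjusting for baseline can move the estimate in either direction.

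**Step 5: illustrative size.** Assume 0.1 to 0.3 degrees of 12-month change per baseline degree, and a systematic imbalance of 2 to 3 degrees within a stratum:
- lower end: 0.1 × 2 = 0.2 degrees, which is 0.2/6.1 = 3% (mild) and 0.2/2.82 = 7% (moderate);
- upper end: 0.3 × 3 = 0.9 degrees, which is 0.9/6.1 = 15% (mild) and 0.9/2.82 = 32% (moderate).

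**The case against.** The defence has several sound parts.

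- **The form of the covariate is not stated.** A reader might infer that Risser adjustment is certainly void. The article does not support that: it never says main effect, and it describes differences in the change of the outcome. If Risser interacts with time, or change is the response, Risser is adjusted for. The choice of term could also be left to a fuller plan. What remains is that the article fixes one covariate, and baseline Cobb and curve site are absent on every reading.
- **Baseline Cobb is not ignored.** It enters through the change score and as the first response in the mixed model, so a stable difference in level is subtracted. The 25-degree split controls it coarsely. The exclusions (apex at T7 or above, complete growth-plate ossification, previous rehabilitation) also limit the range of curve site, maturity and treatment history. This stands; the gap concerns differences within wide strata.
- **Age and sex are handled by matching.** This is largely right by design, although the model does not carry the matching through.
- **Preference may not drive allocation here.** A reader might infer that families choose the arm. The Background reports refusals in earlier trials, and Participant recruitment says only that participants are assigned. Preference-driven selection is a possibility, not a stated fact.
- **Chance imbalance is not confounding.** The standard error already covers it. The 2 to 3 degrees above must be read as a systematic difference, and it is assumed.
- **Baseline adjustment is a judgement in non-equivalent groups.** This stands, as Step 4 shows, and it is why a single replacement model would be too strong a request.

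Nor can a saving in patients be claimed for baseline adjustment. The article gives no correlation between baseline and 12-month values.

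**Conclusion.** The point holds in a limited form. The article calls confounding a key threat, then specifies a model whose only named covariate has no effect on the treatment contrast if entered as a main effect. That result is algebraic with complete two-visit data and nearly holds with missing follow-up. On every reading, within-stratum baseline Cobb and curve site are unadjusted, and age and sex are not in the model.

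The documents do not show that the result will be biased, or by how much. The range of 0.2 to 0.9 degrees rests on an assumed slope and an assumed imbalance. It matters more in the moderate stratum (7-32% of the planned effect) than in the mild one (3-15%), and the direction depends on the sign of the slope. This is an inexpensive improvement worth making before analysis. It does not show that the planned comparison is invalid.

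**What to change.** In each stratum, regress the 12-month largest Cobb angle (or its change, which gives the same group coefficient once baseline is a covariate) on group, baseline largest Cobb angle, Risser sign, age, sex and apex level. Alternatively, keep the mixed model and enter Risser sign, age, sex and apex level each with its time interaction.

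Because the groups are non-equivalent, also report as a sensitivity analysis the change-score estimate adjusted for Risser sign, age, sex and apex level but not for baseline Cobb. With complete data the mixed-model alternative gives this same estimate, so if that is chosen as primary, the baseline-adjusted regression should be the sensitivity analysis. State in advance which is primary.

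The cost is a change of wording and a few degrees of freedom in strata of 52 and 62 evaluable patients. No new data should be needed: curve size and apex can be read from the first-visit X-ray, Risser sign is already planned, and age and sex belong to the basic information on the case report form.
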